## Abstract

**Background:**

Despite the numerous healthcare smartphone applications for self-management of diabetes, patients often fail to use these applications consistently due to various limitations, including difficulty in inputting dietary information by text search and inconvenient and non-persistent self-glucose measurement by home glucometer. We plan to apply a digital integrated healthcare platform using an artificial intelligence (AI)-based dietary management solution and a continuous glucose monitoring system (CGMS) to overcome those limitations. Furthermore, medical staff will be performing monitoring and intervention to encourage continuous use of the program. The aim of this trial is to examine the efficacy of the program in patients with type 2 diabetes mellitus (T2DM) who have HbA1c 53–69 mmol/mol (7.0–8.5%) and body mass index (BMI) ≥ 23 mg/m^2^.

**Methods:**

This is a 48-week, open-label, randomized, multicenter trial consisting of patients with type 2 diabetes. The patients will be randomly assigned to three groups: control group A will receive routine diabetes care; experimental group B will use the digital integrated healthcare platform by themselves without feedback; and experimental group C will use the digital integrated healthcare platform with continuous glucose monitoring and feedback from medical staff. There are five follow-up measures: baseline and post-intervention at weeks 12, 24, 36, and 48. The primary end point is change in HbA1c from baseline to six months after the intervention.

**Discussion:**

This trial will verify the effectiveness of a digital integrated healthcare platform with an AI-driven dietary solution and a real-time CGMS in patients with T2DM.

**Trial registration:**

Clinicaltrials.gov NCT 04161170, registered on 08 November 2019.

https://clinicaltrials.gov/ct2/show/NCT04161170?term=NCT04161170&draw=2&rank=1

## Background

Diabetes mellitus is one of the most common chronic diseases and incurs extensive social and economic costs. According to the International Diabetes Federation (IDF), there were approximately 463 million people (20–79 years) with diabetes globally in 2019, and the number is expected to rise to 700 million by 2045 [1]. It is widely known that not only medications, but also lifestyle managements such as diet, exercise, and weight control, are essential in the treatment of diabetes [2–4]. Recently, advances in mobile technology have led to a large number of smartphone applications (apps) that aim to facilitate self-management of diabetes mellitus (DM) [5–8].

Although numerous healthcare apps have been developed for patients with diabetes, few of them are consistently used due to limitations. First, it is inconvenient to input multiple dietary data points. Dietary control is important in diabetes management, so feedback based on the dietary record is required. However, patients often struggle to record their dietary information reliably because it is difficult to search and enter every food item eaten into the smartphone healthcare apps. In addition, it is hard to convert the various entered foods into actual dietary data such as nutritional composition and calories. Moreover, because values of blood glucose measured by a home glucometer have to be manually entered into the apps, there are multiple opportunities for typographical errors in the glucose records. Recently, Bluetooth technology has allowed for values of blood glucose by a glucometer to be automatically recorded in any linked smartphone apps. However, due to the discomfort of the finger-prick blood test, patients do not often measure their blood glucose level. Also, most diabetes self-management apps require users to assess their body weight, blood pressure, and amount of exercise using a scale, sphygmomanometer, and pedometer, respectively, and then manually input those values. Although some healthcare apps can now be linked to devices via Bluetooth so that health information is automatically recorded into the apps, various biometric data such as blood glucose level, body weight, blood pressure, and amount of exercise are not integrated and must be provided separately for management of diabetes. In addition, most patients are inconsistent in use of these apps on their own without feedback from medical staff.

Therefore, in this study, we plan to verify the clinical effect of the digital integrated healthcare platform, which is designed to overcome these limitations using clinical intervention. First, using an artificial intelligence (AI)-driven diet management program called “FoodLens,” the only input is a single photograph of the meal prior to eating; the program then identifies all the food contents and determines the individual amounts of each in the photograph. There is no need for text search, making it considerably more convenient for users. Considering the low rate of self-assessed blood glucose level, continuous blood glucose monitoring (CGM) for 1 week every 3 months will be performed to provide blood glucose level without a finger prick. A Bluetooth-enabled glucometer, scale with bioelectrical impedance analysis, sphygmomanometer, and watch-type pedometer are each paired with the integrated platform to automatically input biometric data such as blood glucose level, body weight, body fat mass, blood pressure, and amount of exercise into the integrated platform, “Auto-check.” All the collected health information will be monitored by medical staff, who will regularly provide personal education and feedback regarding weight control, dietary plan, and exercise to the subjects.

The aim of this study is to investigate the efficacy of a digital, integrated healthcare platform using an AI-based dietary management solution and a continuous glucose monitoring system in patients with type 2 diabetes mellitus (T2DM).

## Methods

### Hypotheses

Our primary hypothesis is that the integrated healthcare platform user group with or without monitoring and feedback by medical staff will show more improved hemoglobin A1c after 6 months of intervention compared to the routine care group. Our secondary hypothesis is that the healthcare platform user group will show greater improvement in HbA1c after 12 months of intervention, improved glycometabolic parameters (Diabetes Treatment Satisfaction Questionnaire [DTSQ] score, body weight, body fat mass, amount of exercise, dietary information, lipid profile, and CGM metrics), and fewer hypoglycemic events or complications after 6 or 12 months of intervention relative to the routine care group.

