### Study design

This is a 48-week, open-label, randomized, multicenter clinical trial conducted in three different university-affiliated hospitals in Seoul, Republic of Korea: Samsung Medical Center, Asan Medical Center, and Kyung Hee University Hospital. Subjects with T2DM will be randomly assigned to three groups in a 1:1:1 ratio. The control group “A” will receive routine diabetes care, with hospital visits every 3 months. Subjects in experimental group “B” will be introduced to the digital integrated healthcare platform to use at home without monitoring or assistance from medical staff. Subjects in experimental group “C” will be introduced to and educated on the healthcare platform for use and application at the hospital. Group C, unlike other groups, will also apply a CGMS for 1 week every 3 months. The medical staff will monitor the integrated healthcare data of group C subjects, including body weight, blood glucose, amount of exercise, and diet information, and will provide personal educational feedback via text message once a week. All subjects will visit a hospital at baseline and every 12 weeks thereafter for a total of 48 weeks (i.e., at week 12, 24, 36, and 48) and undergo a physical examination, blood and urine laboratory tests, and a Diabetes Treatment Satisfaction Questionnaire (DTSQ) at every visit. Figure 1 shows an overview of the study.

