### Outcome variables

The primary outcome will be change in HbA1c from baseline to 6 months after intervention.

The main secondary outcome will be levels of HbA1c and fasting blood glucose at weeks 12, 24, 36, and 48. Other secondary outcomes include lipid profile (i.e., total cholesterol, high-density lipoprotein [HDL] cholesterol, triglycerides, and low-density lipoprotein [LDL] cholesterol) at weeks 24 and 48; the incidence of hypoglycemic events and adverse events at weeks 12, 24, 36, and 48; satisfaction evaluation according to the Diabetes Treatment Satisfaction Questionnaire (DTSQ) [9, 10] at weeks 12, 24, 36, and 48; mean body weight, BMI, and body fat mass for 1 week prior to weeks 12, 24, 36, and 48; mean number of steps, burned calories, and walking distance for 1 month prior to weeks 12, 24, 36, and 48; and mean calorie intake for 3 consecutive days prior to weeks 12, 24, 36, and 48. For experimental group C, secondary outcomes also include CGM metrics, specifically the values of mean glucose; coefficient of variation (CV); and percentages of time in range (TIR), time above range (TAR), and time below range (TBR) for 1 week prior to weeks 12, 24, 36, and 48, and the number of educational interventions by medical staff at weeks 12, 24, 36, and 48.

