### Sample size assumptions

Assuming a 0.3% difference in HbA1c values between the study groups (mean HbA1c 58 mmol/mol (7.44%) [standard deviation, 0.6%]) (effect size d = 0.50) according to previous studies, [7, 11] 78 subjects per group are required, with a two-sided alpha threshold of 0.05 and 80% power. Considering a dropout rate of 20%, the total number of patients required for this study is estimated to be 294 (98 patients per group) from the collective three hospitals.

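### The primary hypothesis spans two active arms without naming the comparisons, and the printed two-sided alpha of 0.05 gives 64 per group, not the stated 78, which matches 0.025 per comparison

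*Protocol article*

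**What the plan says.** All references are to the protocol article.

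- **Hypotheses:** one primary hypothesis, "Our primary hypothesis is that the integrated healthcare platform user group with or without monitoring and feedback by medical staff", set against the routine care group for HbA1c after 6 months.
- **Study design:** "Subjects with T2DM will be randomly assigned to three groups in a 1:1:1 ratio". A is routine care, B uses the platform alone, and C uses it with staff feedback and periodic continuous glucose monitoring.
- **Outcome variables:** "The primary outcome will be change in HbA1c from baseline to 6 months after intervention". No contrast between arms is named here.
- **Sample size assumptions:** "Assuming a 0.3% difference in HbA1c values between the study groups", with "standard deviation, 0.6" (in % HbA1c) and "effect size d = 0.50", leading to "78 subjects per group are required, with a two-sided alpha threshold of 0.05 and 80% power". A 20% dropout allowance then gives 98 per group and 294 in total.
- **Data analysis:** two-sample tests are listed for baseline comparisons and paired tests for change within a group.

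**The concern.** There is no single randomised platform-user group. There are two arms carrying different claims: a self-used app, and an app with dietitian feedback and glucose monitoring. The hypothesis can be read in three ways (B or C beats A, both beat A, or B and C pooled beat A), and each is a different decision rule with its own error rate. The only threshold a reader has is the 0.05 in the sample size section, and it is not said whether that is an overall level or a level per comparison.

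The sample size is the one place where the intended per-comparison level can be checked against a number. If 78 does not follow from 0.05, then the printed threshold is probably not the one used to size the trial. Someone applying it as printed could test each arm at 0.05 and report success of one arm as success of the platform.

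**Working it through.** **Inputs** (Sample size assumptions, Study design): difference 0.3% HbA1c, SD 0.6%, so d = 0.3/0.6 = 0.50, as printed. Two-sided alpha 0.05, power 80%, 78 per group, dropout 20%, allocation 1:1:1.

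**1. The stated size.** For two equal groups, n per group = 2(z₁₋α/₂ + z₀.₈₀)²/d².

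- α = 0.05: 2(1.960 + 0.842)²/0.25 = 62.8, so 63. The exact t-test calculation gives 64 (power 80.1%).
- α = 0.025: 2(2.241 + 0.842)²/0.25 = 76.0, so 77. The exact t-test gives 78 (power 80.4%; 77 gives 79.8%).
- α = 0.05/3: 84 by the normal formula, 86 by exact t.
- 78 per group tested at α = 0.05 has 87% power, not 80%.

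The printed inputs therefore do not reproduce 78. Replacing 0.05 by 0.025 reproduces it exactly.

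**2. Dropout step.** 78/(1 − 0.20) = 97.5, so 98 per group, and 3 × 98 = 294. This agrees with the article. Starting from 64 it would be 64/0.80 = 80 per group and 240 in total.

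**3. Error rate under each reading.** The B−A and C−A differences share the control mean. Their covariance is σ²/n and each has variance 2σ²/n, so their correlation is 0.5. With no true effect in either arm, the bivariate normal gives:

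| Decision rule | Result |
|---|---|
| Either arm, each at two-sided 0.05, error in any direction | 0.05 + 0.05 − 0.0093 = 9.1% |
| Same rule, false claims of benefit only | 0.025 + 0.025 − 0.0046 = 4.5% |
| Either arm, each at two-sided 0.025, any direction | 4.6% (bound 5%) |
| Both arms must beat A, each at two-sided 0.05 | 0.5% false claim of benefit |
| B and C pooled vs A, one test | 5% |

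A simulation of 100,000 trials with t-tests at n = 78 gave 9.05% for the first row and 4.63% for the third.

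**4. Could another design explain 78?**

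- *Pooled B + C vs A* at 0.05 with 2:1 numbers: control n = 1.5(1.960 + 0.842)²/0.25 = 47.1, so 48. Not 78.
- *Both arms required*, each at 0.05, with 80% power to win both when d = 0.50 in each. At n = 78 the expected z is 0.5√(78/2) = 3.12. With correlation 0.5, the chance that both exceed 1.96 is 79.8% (normal; about 79.3% by t-test simulation). Reaching 80% takes 79 (normal) or 80 (t). Close, but not 78.
- *Three-group ANOVA* at 0.05 with means spaced 0, 0.25 and 0.5 SD: 79 per group (79.95% power at 78). Close, but the article names no such test.

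**The case against.** A reader might infer that the trial runs a 9% false-positive rate. The article does not support that as a flat statement. The figure needs both an either-arm rule and each test at the full 0.05, and neither is fixed. The hypothesis is worded in the singular, so pooling is a fair reading, and so is requiring both arms. It is also directional, and on that footing the chance of a false claim of benefit is 4.5%. The stated size itself points towards a split, not away from one.

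Nor can the Data analysis section be used to show that B vs A and C vs A will each be tested at 0.05. Its two-sample tests are for baseline comparisons. A multiplicity rule may well stand in the full protocol or the analysis plan, and its absence from an article is not a fault.

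The inference of a split is not proof. A both-arms rule with 80% joint power, or an ANOVA with evenly spaced means, comes within one or two patients of 78.

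All of this stands and limits the point. It does not remove what the article does state: an alpha and a sample size that disagree under the two-group effect size it gives, and a hypothesis whose wording leaves open which comparisons that alpha governs.

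**Conclusion.** The point holds in limited form. The demonstrable defect is that d = 0.50, two-sided 0.05 and 80% power give 64 per group, not 78. The printed 78, 98 and 294 follow exactly from 0.025 per comparison with a two-sample t-test. That a two-way split was intended is an inference from the arithmetic.

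The error-rate consequence is conditional: up to about 9.1% two-sided if either arm can carry the hypothesis at 0.05 each, 4.6% at 0.025 each, and no inflation under the pooled or both-required readings. These figures assume equal group sizes, approximately normal test statistics and no true effect in either arm.

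**What to change.** In Hypotheses, name B vs A and C vs A on change in HbA1c to week 24 as the two primary comparisons, and limit any claim to the arm whose comparison passes. In Sample size assumptions, state two-sided 0.025 for each comparison (or Holm) with a family-wise two-sided level of 0.05, and say that 78 per group gives 80% power at 0.025 per comparison. If the full protocol or analysis plan already has this rule, bring the article's wording into line with it. If the sponsor instead means the pooled contrast or requires both arms to succeed, say so and give the calculation that leads to 78.

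The cost is a few sentences, settled before outcome data are compared between arms. No more patients are needed, because 78, 98 and 294 stand unchanged. The downside is a stricter threshold per comparison than the 0.05 now printed, with power of 80% per comparison instead of 87%.

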### Data collection and intervention

#### Demographic and medical survey

The following demographic and medical information will be collected (Table 1): age, sex, smoking history, past and present medical history (e.g., duration of T2DM, hypertension, cardiovascular disease, liver disease, dyslipidemia), diabetes medication and other concomitant medication including steroids and statins during the 12 weeks prior to screening, and frequency of self-monitoring of blood glucose in the recent month.

**Table 1 Tab1:** Study schedule

Study procedure	Screening	Baseline	12 weeks	24 weeks	36 weeks	48 weeks	Early termination
Visit	1	2	3	4	5	6	EDV
Visit window	−28 ~ 0 day	0	±14 days	±14 days	±14 days	±14 days	
Informed consent	**●**						
Demographic information and medical history	**●**						
Inclusion/exclusion criteria	**●**						
Physical examination	**●**						
Randomization		**●**					
Digital integrated healthcare platform application (Groups B, C)		**●**	**●**	**●**	**●**	**●**	**●**
Continuous glucose monitoring system application (Group C)		**●**	**●**	**●**	**●**	**●**	**●**
Continuous glucose monitoring system data collection (Group C)		**●**	**●**	**●**	**●**	**●**	**●**
Vital signs	**●**	**●**	**●**	**●**	**●**	**●**	**●**
Laboratory tests	**●**	**●**	**●**	**●**	**●**	**●**	**●**
Evaluation of hypoglycemia/severe hyperglycemia		**●**	**●**	**●**	**●**	**●**	
Satisfaction questionnaire (DTSQ)	**●**		**●**	**●**	**●**	**●**	**●**
Digital integrated healthcare platform data collection (Group B, C)		**●**	**●**	**●**	**●**	**●**	**●**
Monitoring and intervention (Group C)		**●**	**●**	**●**	**●**	**●**	**●**
Adverse event report		**●**	**●**	**●**	**●**	**●**	**●**
Concomitant drugs	**●**	**●**	**●**	**●**	**●**	**●**	**●**

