### Anthropometric and vital sign measurements

At each clinical visit, vital signs including blood pressure, heart rate, and, body weight, and BMI will be collected.

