### Distribution and use of at-home measurement devices and the digital integrated healthcare platform

For subjects in experimental groups B and C, at-home measurement devices of a Bluetooth-enabled glucometer, scale with bioelectrical impedance analysis, sphygmomanometer, and watch-type pedometer will be provided. Subjects in group B will configure and apply these devices and the platform by themselves, while subjects in group C will be provided instruction regarding the configuration and use of the devices and the platform by medical staff during their hospital visit.

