### Data acquisition by the digital integrated healthcare platform

For subjects in group C, the following data will be collected from the indicated devices, all Bluetooth-enabled, and recorded on the digital integrated healthcare platform: glucose level from the glucometer; body weight, BMI, and body fat mass measured by a scale with bioelectrical impedance analysis; blood pressure by sphygmomanometer; number of steps, burned calories, and walking distance assessed by a watch-type pedometer; and intake calories assessed by the AI-based dietary management solution. Subjects in group C will be able to access their integrated data via the smartphone app, and medical staff can also access the data on the platform.

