### Glucose data by continuous glucose monitoring system

Subjects in group C will apply a CGMS for 1 week prior to the hospital visit at weeks 12, 24, 36, and 48. CGM metrics comprise values of mean glucose; CV; and percentages of time in range (TIR), time above range (TAR), and time below range (TBR) during that week will be collected.

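### Four measures in the secondary hypothesis (fat mass, exercise, diet, CGM) have no described source in the routine-care arm, and the weight outcome is defined in a form that arm cannot supply

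*Protocol article*

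**What the plan says.** The Hypotheses section lists DTSQ score together with "body weight, body fat mass, amount of exercise, dietary information, lipid profile, and CGM metrics", and claims an advantage in them "after 6 or 12 months of intervention relative to the routine care group".

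The sections on measurement describe the following.

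- **Devices.** "For subjects in experimental groups B and C, at-home measurement devices of a Bluetooth-enabled glucometer, scale with bioelectrical impedance analysis", a sphygmomanometer and a pedometer are provided. Group A is not mentioned. The Dietary data section likewise names only B and C, and Table 1 labels platform data collection as B and C.
- **Weight, BMI and fat mass outcome.** Outcome variables gives "mean body weight, BMI, and body fat mass for 1 week prior to weeks 12, 24, 36, and 48". Activity is a one-month mean and calorie intake a three-day mean. None of these is restricted to particular arms.
- **Clinic measurements.** "At each clinical visit, vital signs including blood pressure, heart rate, and, body weight, and BMI will be collected". No arm is singled out, and Study design has all subjects attending every 12 weeks.
- **CGM.** Study design and Outcome variables both confine it to group C. The CGM section says "Subjects in group C will apply a CGMS for 1 week prior to the hospital visit at weeks 12, 24, 36, and 48", while the Table 1 row beginning "Continuous glucose monitoring system data collection (Group C" is also marked at baseline.
- **Platform data.** The Data acquisition section opens with "For subjects in group C, the following data will be collected from the indicated devices" and does not mention group B.

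**The concern.** A hypothesis of benefit over routine care needs the same measurement in the routine-care arm. For fat mass, exercise, diet and CGM metrics, the article assigns the measuring instrument to the experimental arms alone. What remains is a description of B and C after randomisation, which cannot support a claim against A.

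For weight, the risk is losing a randomised comparison that the trial already collects data for. Weight is a central outcome of a lifestyle intervention in patients selected for a BMI of at least 23. If the outcome is taken literally as a one-week mean, group A drops out of it even though its clinic weights are on file.

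**Working it through.** No figure in the plan needs to be reproduced here. The check sets each of the seven measures in the secondary hypothesis against the arms in which the article says it is measured.

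| Measure | A | B | C | Where described |
|---|---|---|---|---|
| DTSQ | yes | yes | yes | Study design; Questionnaire section |
| Lipid profile | yes | yes | yes | Study design; Laboratory tests |
| Weight (and BMI), clinic value | yes | yes | yes | Anthropometric section; Study design |
| Weight (and BMI), one-week mean | no | yes | yes | Outcome variables; device distribution |
| Body fat mass | no | yes | yes | Device distribution; Table 1 |
| Exercise (steps, burned calories, distance) | no | yes | yes | Device distribution; Table 1 |
| Diet (calorie intake) | no | yes | yes | Dietary data; Table 1 |
| CGM metrics | no | no | yes | Study design; Outcome variables; Table 1 |

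**Count.** Weight takes two rows but is one measure, so the table covers seven. Four (fat mass, exercise, diet, CGM) have no described group A source. One (weight) has group A data, but not in the form in which the outcome is defined. Two (DTSQ, lipids) raise no problem.

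**CGM.** Group B has no CGM either, so a platform-user group combining B and C cannot be formed for these metrics.

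**Group B.** The table follows Table 1 and the device and dietary sections. If the Data acquisition section, which names only C, were the governing text, fat mass and activity could not be compared between B and C either. The diet measure would keep its B data through the Dietary data section.

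**Baseline.** Outcome variables defines the averaging windows only before weeks 12, 24, 36 and 48. Table 1 starts the platform at the baseline visit and also marks platform and CGM data collection there. The Data analysis section plans paired tests of change from baseline in each group. The article does not say what the baseline value of a one-week, one-month or three-day mean is, nor whether it comes before the intervention.

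**Numbers for a three-arm weight comparison.** The Sample size section gives 98 per arm and 20% dropout: 98 × (1 − 0.20) = 78.4, so about 78 evaluable per arm.

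**The case against.** The strongest reply concerns weight. A reader might infer that five of the seven measures lack control data, counting weight among them. The article does not support that: clinic weight and BMI are collected at every visit without restriction by arm, and the hypothesis says only body weight, which group A can supply. The objection stands, and the point on weight is confined to the mismatch of definitions.

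Second, Outcome variables never says that its means are home readings. Tying them to the devices is an inference. It is a strong one, because no other source of a one-week, one-month or three-day mean is described.

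Third, Outcome variables already limits CGM metrics to group C, so the CGM defect lies in the wording of the hypothesis. A reader might go on to infer that the CGM results will be offered as superiority over routine care; the outcome definition points the other way.

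Fourth, a reader might infer that the device measures have no pre-intervention value at all. The baseline marks in Table 1 do not allow so flat a statement. The value is undefined, not shown to be absent. For the same reason, before-and-after description cannot be taken for granted as a fallback.

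Finally, the article condenses a fuller protocol, which might give group A a separate measurement. That would answer the point, but the issue here is not mere silence: the article assigns instruments and schedule rows to named arms, and its hypothesis conflicts with that assignment.

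**Conclusion.** The point holds in this limited form. For fat mass, exercise, diet and CGM metrics, the secondary hypothesis against routine care cannot be tested from the measurements described. For weight and BMI, the comparison is feasible from clinic values, but the defined outcome does not use them. That is four of seven measures without control data and one with an unsuitable definition.

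The conclusion assumes that the weight, activity and calorie means come from the devices and the diet app, and that group A receives neither. It concerns secondary outcomes only; HbA1c is measured in every arm. The disagreements over group B platform data and baseline CGM are smaller, separate inconsistencies, but they determine what can be said about B versus C and about change within C.

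**What to change.** 1. For the comparison with routine care, define the weight and BMI outcome as change from baseline in the clinic-measured value in all three arms. Keep the one-week means as supplementary in B and C.
2. Limit fat mass, steps, burned calories, walking distance and calorie intake to B versus C. Add a caveat for calorie intake: group C alone has three-day periods of intensified dietary support with daily messages, at 12-week intervals. The article does not say whether these coincide with the three-day outcome windows. If they do, intake in C is recorded under prompting that B does not receive.
3. Take CGM metrics out of the hypothesis against routine care and report them descriptively within C, in line with Outcome variables.
4. Reconcile the Data acquisition section (C only) with Table 1 and the device and dietary sections (B and C). Reconcile the CGM section (before weeks 12 to 48) with Table 1 (baseline also marked). State whether each device measure has a baseline value and how it is formed.

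No new visits, devices or participants are needed, because clinic weight and BMI are already collected. Redefining a secondary outcome does require a minor protocol amendment, and the trial will make fewer secondary claims against routine care.
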